## Abstract

**Background:**

Sarcopenia, characterised by declines in muscle mass and function, is expected to impact many postmenopausal women due to ageing and sedentary lifestyles. Hormonal changes during menopause exacerbate loss of lean mass, visceral fat gain, and risk of cardiometabolic disease. Resistance and high-intensity interval training (HIIT) are effective countermeasures, with adequate protein and fibre intake essential to support favourable adaptations. However, many women fall short of these protein and fibre dietary recommendations, particularly at breakfast. Defatted almond protein powder (APP), a by-product of almond oil production, is rich in protein and fibre and may enhance exercise-induced adaptations, though its effects remain untested.

**Methods:**

This protocol outlines a 12-week study comprising a 10-week supervised resistance and HIIT intervention, with baseline and post-intervention assessments conducted over one-week periods immediately before and after the intervention. The randomised, double-blind, placebo-controlled trial will investigate the effects of defatted APP supplementation in postmenopausal women. We aim to recruit 48 participants who will be randomly allocated to receive either APP or an energy-matched placebo (maltodextrin). Primary outcomes include changes in total and regional lean mass which will be assessed using dual-energy X-ray absorptiometry (DXA). Secondary outcomes include strength, assessed via 3-repetition maximum (3-RM) chest press and leg press, and maximal handgrip strength; cardiovascular fitness (VO₂peak); total body fat (absolute and %), blood lipids; blood glucose; insulin response; appetite; supplement acceptability; and dietary intake. Data will be analysed using linear regression and mixed-effects models under intention-to-treat and per-protocol frameworks.

**Discussion:**

This study will be the first to examine the effects of daily supplementation with APP on musculoskeletal and metabolic outcomes in postmenopausal women undergoing structured and supervised exercise training. Findings of this study may assist in developing applications for high protein/fibre by-product from the nut/seed oil industry and determine if supplementation with this almond derived product is an effective nutritional strategy to support training adaptations to strength and HIIT training in ageing women.

**Trial registration:**

ANZCTR: ACTRN12625000133437 (Date Registered: 06 February 2025). Registration URL: ANZCTR Trial Registration.

**Ethics: DUHREC: (2024/HE000126).**

**Version: 2.0 date (16/02/2026).**

**Supplementary Information:**

The online version contains supplementary material available at 10.1186/s12937-026-01330-w.

## Introduction

### Background and rationale

The global number of individuals aged ≥ 60 years is projected to double from 1.1 billion in 2023, to more than 2.1 billion by 2050 [1]. While females tend to live longer than males, they face nearly twice the risk of disability and incur a greater burden of chronic disease [2, 3]. This sex-based difference in disease burden may be driven (at least in part) by menopause. Menopause is associated with accelerated loss of fat-free mass and increases in visceral and subcutaneous adipose tissue [4–6]. These changes are linked to elevated cardiometabolic risk factors including increased blood pressure, low-density lipoprotein cholesterol (LDL-C), and obesity [5, 7]. Excess visceral fat contributes to cardiovascular disease through insulin resistance, systemic inflammation, and lipid dysregulation [8]. In parallel, ageing is associated with a progressive decline in strength, physical function and skeletal muscle mass (i.e., sarcopenia), which contributes to frailty, disability and loss of independence in older adults [9]. To mitigate these age- and menopause-related declines, evidence suggests that a combination of targeted exercise training and strategic nutrition approaches may support healthy aging [10, 11]. In particular, dietary protein and fibre intake may help preserve musculoskeletal and metabolic health respectively, in post-menopausal women [9, 12].

Exercise-based strategies, including resistance training and high-intensity interval training (HIIT) are effective in improving body composition, physical capacity and cardiometabolic health in postmenopausal women [13, 14]. Resistance training enhances muscular strength and lean mass in a dose-dependent manner, while also improving metabolic markers such as LDL-C [15, 16]. HIIT, characterised by alternating periods of vigorous intensity exercise and rest periods, improves cardiovascular fitness, and has been shown to reduce visceral fat and blood pressure, while also improving lipid profiles and blood glucose control in postmenopausal women [17, 18]. These adaptations may be enhanced by nutritional strategies that support muscle protein synthesis (MPS) and metabolic health following menopause.

While dietary protein is critical for maximising MPS in response to exercise, ageing is associated with anabolic resistance, a blunted sensitivity of skeletal muscle to protein intake [19–21]. To counteract anabolic resistance, daily protein intake recommendations for older adults have been revised upward to at least 1.2 g per kilogram (g/kg) of body mass (BM), with 20 to 30 g per meal suggested to maximise MPS, especially in the context of post-training recovery [22, 23]. A 2018 Australian national report estimated that the average protein intake for females aged 19 to 70 years was 79 g/day, equivalent to approximately 1.1 g/kgBM based on an average weight of 71 kg [19]. While this exceeds the Estimated Average Requirement (EAR) of 0.6–0.7 g/kgBM for nitrogen balance, it may still be insufficient to support muscle preservation and prevent sarcopenia in ageing populations [22]. Furthermore, protein intake is often skewed toward the evening meal, with breakfast and lunch typically providing only 10–18 g and 14–18 g, respectively, amounts that are suboptimal for stimulating MPS earlier in the day [19, 21, 24, 25]. Therefore, postmenopausal women may benefit from supplementing their diet with protein, particularly early in the day.

In addition to suboptimal protein intake, national survey data indicate that postmenopausal women are also consuming inadequate amounts of dietary fibre [21, 26]. Dietary fibre intakes for women > 50 years are reported as 21–22 g/day, which falls well below the suggested target of 28 g per day for optimal health benefits [27]. Soluble fibres slow gastric emptying and form viscous gels in the gut, reducing postprandial glucose and insulin spikes [28]. Fermentable fibres are metabolised by gut microbiota into short-chain fatty acids (SCFAs), such as butyrate, which have been linked to improved insulin sensitivity, reduced systemic inflammation, and better lipid metabolism [29, 30]. Fibre intake has also been associated with reduced LDL-C, enhanced satiety, and healthier body composition, all of which are important in reducing the risk of cardiovascular disease and type 2 diabetes risk in ageing women [31–33]. Therefore, optimising fibre intake may complement the benefits of exercise and protein intake in improving metabolic health and physical functional outcomes in postmenopausal women.

While animal-based proteins have traditionally been considered superior for MPS, plant-based proteins including soy, pea, and rice, can be equally effective if consumed in adequate amounts [34, 35]. Emerging evidence suggests that nut-based protein powders, such as defatted almond protein powder (APP), may provide an alternative plant protein source with additional cardiometabolic benefits [36–38]. APP is produced as a by-product of almond oil extraction, which results in a protein- and fibre-rich ingredient with a substantially reduced energy content [39]. This nutritional profile may be particularly beneficial for post-menopausal women, who typically have low energy requirements yet would benefit from additional protein. Despite the potential of APP as a nutritional supplement, its effects on exercise-induced adaptations remain unexplored.

## Objectives

The primary objective of this study is to evaluate the additive effects of defatted APP, beyond those induced by exercise training alone, on lean muscle mass in postmenopausal women undertaking a 10-week, fully supervised resistance and high-intensity interval training (HIIT) program.

Secondary outcome measures include between-group differences in muscular strength and aerobic fitness; body composition (including total and regional fat mass); cardiometabolic health markers, including blood glucose and insulin sensitivity, derived from an oral glucose tolerance test (OGTT) and calculated using validated surrogate indices (e.g. the Matsuda insulin sensitivity index and/or HOMA-IR derived from fasting values); lipid profiles; appetite regulation and taste preference; and dietary intake patterns, with a specific focus on protein and fibre intake.

Given that both groups complete an identical exercise intervention, all secondary outcomes will be interpreted as reflecting the incremental contribution of APP supplementation, relative to an energy-matched placebo, rather than the independent effects of exercise or fibre alone. Outcomes will be assessed at baseline and following the 10-week intervention.

### Methods: study design and setting

This study is a 12-week, randomised, double-blind, placebo-controlled trial, which includes baseline and post-intervention assessment weeks (Week 1 and Week 12) and a 10-week supervised training and supplementation phase (Weeks 2–11) (Fig. 1). After the participants consume their first supplement in week 2, acceptance and supplement-related appetite responses will be measured.

**Fig. 1 Fig1:**
[figure not shown]
Schematic of experimental timeline illustrating the test weeks and the training weeks in addition to the test-day timeline illustrating the testing procedures. Abbreviations: 3-RM: 3 repetition maximum, APP: Almond Protein Powder, DXA: Dual-energy X-ray absorptiometry, HIIT: High-intensity interval training, OGTT: Oral glucose tolerance test, RT: resistance training. Figure adapted from [40]

### Overall experimental protocol

A detailed overview of the study timeline, including testing and training phases and procedures is presented in Fig. 1. The trial will take place at the Deakin University, Burwood campus (Melbourne, Australia), within a supervised, university-based laboratory setting and adheres to the Standard Protocol Items: Recommendations for Intervention Trials (SPIRIT, Appendix 1) [40]. Recruitment commenced in March 2025 and data collection is expected to finish in October 2026. This study design, including all participant consent forms and research tools, has been reviewed and approved by the Deakin University Human Research Ethics Committee (Approval Number: 2024/HE000126). Organisational consent was obtained to recruit within Deakin University. The trial has also been prospectively registered with the Australian New Zealand Clinical Trials Registry (ANZCTR) (ID: ACTRN12625000133437).

## Eligibility criteria

### Recruitment and consent

Participants will be recruited using physical posters displayed on university campuses, community centres, and fitness facilities, as well as targeted online advertisements via social media platforms and institutional mailing lists. Online advertisements will target women aged 50–65 years residing in metropolitan Melbourne and surrounding areas.

Interested individuals will be directed to an online expression of interest form via Research Electronic Data Capture (REDcap). This form includes a Plain Language Statement (PLS) outlining the purpose, procedures, risks, and benefits of the study. After reviewing the PLS, individuals will be required to provide electronic informed consent via REDcap before submitting any personal information or completing the eligibility screening questionnaire. Electronic consent will be obtained by participants actively selecting consent statements and providing an electronic signature, in accordance with Deakin University Human Research Ethics Committee (DUHREC) approved procedures. Eligible participants identified through the online screening process will be contacted by a member of the research team via email or phone to confirm eligibility, answer any additional questions, and schedule laboratory visits. At the first laboratory visit, participants will be given the opportunity to ask further questions, and verbal confirmation of consent will be reconfirmed prior to the commencement of any study procedures. Participants will be informed that participation is voluntary and that they may withdraw from the study at any time without penalty or consequence.

Participants will be eligible for inclusion into the study if they meet the following criteria:

Aged 50–65 years oldClassified as overweight (25–29.9 kg/m²) or obese class I (30–34.9 kg/m²)For participants who identify as being of Asian ethnicity, we will also apply WHO-recommended Asian-specific BMI thresholds to better reflect known differences in body composition and metabolic risk:
◦ Overweight Asian-threshold: BMI 23.0–24.9 kg/m²◦ Obese Asian-threshold: BMI ≥ 25.0–29.9 kg/m² [41]
Postmenopausal, defined as natural, medical or surgical menopause with no menstrual bleeding for ≥ 12 months.Not currently engaged in progressive resistance or balance/mobility training (≥ 1 session per week) for the past 6 months.Weight stable (no more than ≤ ± 2 kg weight change over the previous 2 months).Not currently using hormone therapy, or using hormone therapy continuously for ≥ 12 months.No history of nut allergies.No uncontrolled hypertension (defined as resting blood pressure ≥ 140/90 mmHg or requiring recent medication changes).No history of thyroid conditions, neuromuscular or skeletal disorders, or clotting disorders.Not undergoing treatment for conditions that affect muscle mass (e.g., cancer treatment, anabolic steroids).No chronic disease affecting nutrient absorption (e.g., cancer, diabetes, cardiovascular disease).No injury preventing exercise participation.Non-smokers.

Participants will complete a Physical Activity Readiness Questionnaire (PAR-Q) as a self-screening tool to identify individuals who may require medical clearance before engaging in physical activity. Individuals with known cardiovascular conditions, high-risk factors, or concerning responses in the PAR-Q may require clearance from a doctor before starting an exercise program.

To help promote study retention, participants will also receive a $100 electronic gift card upon the completion of the study. There is no patient or public involvement planned in the design, conduct, or reporting of this trial due to the controlled nature of the intervention and the need for standardised procedures.

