### Blood pressure monitoring and safety procedures

Resting blood pressure (BP) will be assessed once participants are seated and have rested quietly for at least 5 min, prior to commencing the OGTT and exercise testing. BP will be measured using an automatic blood pressure monitor (Welch Allyn ProBP 3400 Series, NY, USA), in accordance with standard clinical guidelines [54]. If resting systolic BP is ≥ 160 mmHg, BP will be re-measured on two additional occasions (total of three measurements), with at least 1–2 min between measurements. If systolic BP remains consistently ≥ 160 mmHg across all readings, testing will be terminated and the participant will be advised to follow up with their general practitioner (GP) and obtain medical clearance prior to proceeding with the 10-week exercise intervention. If systolic BP falls below 160 mmHg in subsequent measurements, testing may proceed with caution.

Blood pressure will also be measured immediately before and immediately after the submaximal bike test (OMRON HEM-7120, OMRON Healthcare Co., Ltd, Kyoto, Japan). If systolic BP is ≥ 160 mmHg at rest prior to exercise, and remains elevated following two confirmatory measurements, the testing session will be terminated and the participant referred to their GP for further investigation.

Participants will also be monitored for hypotension, defined as BP ≤ 90/60 mmHg [54–56]. In such cases, testing will proceed with caution, and participants will be closely monitored for symptoms including dizziness, light-headedness, faintness, or loss of balance. If any of these symptoms are present, OGTT and exercise testing will not proceed, and participants will be advised to seek medical follow-up.

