#### Concomitant care

Participants will be instructed to maintain their habitual diet and physical activity patterns outside of the supervised training sessions for the duration of the study. Initiation of new structured exercise, high-intensity training or formal dietary interventions (e.g., weight loss programs, protein or fibre supplements) outside of the prescribed intervention will also be discouraged. Usual medical care and medications for unrelated health conditions will be permitted, provided they are stable for at least 3 months prior to enrolment and remain unchanged during the study period.

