### Randomisation and blinding

#### Sequence generation

The random allocation sequence will be generated by an independent researcher not otherwise involved in participant enrolment, intervention delivery, or outcome assessment. A stratified block randomised approach will be used. Participants who meet inclusion criteria and consent to participate will be randomly allocated to either the experimental or placebo group after the first laboratory visit.

Randomisation will be stratified according to the following variables:

Hormone replacement therapy use (Yes/No)Appendicular skeletal muscle mass Index (Low/High), determined by baseline DXA scan and classified according to the European Working Group on Sarcopenia in Older People (EWGSOP) cut-offs [9]

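### A confirmed baseline systolic of 160 mmHg or above fails the 140/90 eligibility limit, yet the safety section lets the woman go on to training after GP clearance alone

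*Protocol article*

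**What the plan says.** Two sections of the protocol article set blood pressure limits.

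- **Recruitment and consent (eligibility list).** The criterion is "No uncontrolled hypertension (defined as resting blood pressure" at or above 140/90 mmHg, with "requiring recent medication changes" as an alternative ground. It carries no exception for women cleared by a doctor.
- **Blood pressure monitoring and safety procedures.** Seated resting pressure is taken "prior to commencing the OGTT and exercise testing". A systolic value of 160 mmHg or above is repeated to give three readings. If all stay at or above 160, testing ends, and the woman is advised to see her GP and "obtain medical clearance prior to proceeding with the 10-week exercise intervention". If systolic falls below 160 "in subsequent measurements, testing may proceed with caution". No action is given for systolic 140–159 or for high diastolic pressure.

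Two other places fix the timing. Before the laboratory visit, Recruitment and consent describes an online form, after which women are "contacted by a member of the research team via email or phone to confirm eligibility". Sequence generation then says: "Participants who meet inclusion criteria and consent to participate will be randomly allocated to either the experimental or placebo group after the first laboratory visit".

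**The concern.** The baseline visit is where eligibility on blood pressure can first be checked by measurement, as far as the article describes. The section governing that measurement uses 160 mmHg systolic and never refers back to 140/90. For a confirmed value of 160 or above it goes further and states what the woman must do before starting the intervention, which is a different outcome from being ineligible.

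The stakes are safety and an accurate description of the enrolled population. Staff have two rules for the same reading. A woman who enters faces 2 sessions per week × 10 weeks = 20 training sessions, with resistance loads up to 80% of 1RM (Table 2) and intervals up to 90% of estimated peak power (Table 3). If women above the limit are admitted, a report that describes the sample by the published criterion would be wrong about them.

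**Working it through.** The plan gives no figure to reproduce, and no power or sample-size formula applies. The check is a comparison of the rules at one decision point.

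**Step 1: do the two rules meet at the same moment?** Pre-testing standardisation procedures lists two laboratory visits, baseline and post-intervention, with no separate screening visit. The contacts before baseline are online, by email or by phone. Allocation follows the first visit and is limited to women who meet the criteria. The baseline reading therefore precedes randomisation, and the 140/90 criterion must still hold then.

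**Step 2: what does each rule do with the baseline reading?** (140/90 is read in the usual way, as either value reaching its limit.)

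| Baseline resting reading | Eligibility list | Safety section | Result |
|---|---|---|---|
| Below 140 and below 90 | Criterion met | No action | Consistent |
| Systolic 140–159 | Excluded | No action, or testing continues if a repeat falls below 160 | Silence |
| Diastolic 90 or above, systolic below 160 | Excluded | No high-diastolic rule | Silence |
| Systolic 160 or above on all three readings | Excluded | Testing stopped; GP clearance before the intervention | Conflict |

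The two systolic thresholds are 160 − 140 = 20 mmHg apart.

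**Step 3: is the last row a conflict or only a gap?** The clearance sentence looks ahead to the 10-week intervention, so it can apply only at baseline; at the final visit the intervention is over. It names clearance as the step before proceeding, does not call the woman ineligible, and does not require a later reading below 140/90. Take a confirmed 165/85: under the eligibility list she is a screen failure, and under the safety section she is a participant awaiting clearance. The same reading leads to two outcomes.

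**The case against.** The strongest defence is that the thresholds do different jobs. One decides eligibility. The other is a same-day safety stop that also serves the post-intervention visit, where an eligibility limit has no meaning. A stop set above the entry limit is not in itself inconsistent. The clearance sentence can also be read as a necessary condition that leaves the 140/90 criterion in force.

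Much of this stands, and it limits the point:

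- A reader might infer that women at 140–159 systolic, or with high diastolic pressure, are admitted. The text does not say so. It is silent on both groups, and where it allows matters to continue it speaks of testing, not enrolment. The eligibility list, applied through Sequence generation, still excludes them.
- A reader might infer that the baseline resting reading is the only blood pressure check before training. It is not. Pressure is measured again immediately before the bike test, with its own 160 mmHg confirmation, stop and GP referral. The PAR-Q may also lead to a request for medical clearance.
- A reader might infer that the GP route breaks the medication rules. That assumes a drug change, which the safety section does not mention. The Concomitant care rule, that medication be stable "prior to enrolment and remain unchanged during the study period", is worded for unrelated conditions.

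The defence does not dispose of the clearance sentence. A pure same-day stop would not need to say how a woman gets into the 10-week programme. The sentence does, and it does not return her to the 140/90 limit. The PAR-Q clearance provision is general and does not amend the hypertension definition.

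**Conclusion.** The point holds for one group: women with confirmed systolic of 160 mmHg or above at baseline, who are excluded by the eligibility list and offered entry after clearance by the safety section. For 140–159 systolic and for high diastolic pressure there is an omission that should be closed, not a contradiction.

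The size is minor to moderate. The documents do not say how many women are affected, and the finding does not depend on a count. Supervised sessions, adverse-event review and the clearance step all reduce the risk, but they do not settle who is eligible. A reader might infer damage to the trial's main result. Nothing supports that: blood pressure is not a listed outcome, and no effect on the primary outcome, power or bias is claimed.

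The conclusion rests on two readings: that 140/90 means either value reaching its limit (needed only for the diastolic remark), and that the article's account of the visits is complete as regards blood pressure measurement before randomisation.

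**What to change.** In Blood pressure monitoring and safety procedures, state that the repeated baseline resting reading must be below 140 systolic and below 90 diastolic before randomisation. Treat a confirmed higher reading as ineligible, with re-screening allowed once pressure is controlled on stable medication. Keep 160 mmHg only as a same-day stop for testing at both visits, and remove clearance alone as a way into the intervention.

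If the sponsor does want to admit cleared women above the present limit, the alternative is to amend the eligibility list openly to the intended limit, including a diastolic one.

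Recruitment began in March 2025, so baseline blood pressure records should be checked once, blinded to allocation. Any randomised woman whose baseline reading was 140/90 or above should be reported as an eligibility deviation and kept in the intention-to-treat analysis.

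The cost is a short ethics amendment, one check of existing records, and possibly a few more screen failures.
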